#### Physical fitness

Physical fitness consists of a combination of aerobic fitness, anaerobic fitness, muscle strength, flexibility and agility. Using the FMS for 500 meters the group of subjects will be divided in two sets depending on their mode of locomotion on this distance: wheelchair users and subjects who are able to walk with or without mobility aids. For these two groups, different testing tools will be used, appropriate for the type of locomotion.

Subsequently, within the group of subjects who are ambulatory different levels of mobility can be identified in order to apply a proper testing protocol, see Table 4.

**Table 4 Tab4:** Level of mobility for identifying testing protocol

Category	Level of mobility
I	Subjects with a very low level of mobility (able to walk <400 m in 6 min)
II	Subjects with a low level of mobility (able to walk > 400 m in 6 min)
III	Subjects with average level of mobility: walking indoors and outdoors and climbing stairs without limitations and able to perform gross motor skills including running and jumping
IV	Subjects with an excellent level of mobility, who are used to run at a speed of 8 km/h during their practicing their sports or during competition

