#### Aerobic fitness

In exercise testing peak, oxygen uptake (VO_2peak_) is considered to be the single best indicator of the cardio-respiratory system, often referred to as aerobic fitness. A cardio-pulmonary exercise testing system, the Cortex Metamax 3X (Samcon bvba, Melle, Belgium), will be used for evaluating the respiratory gasses and VO_2peak_.

Bhambani et al. concluded that maximal exercise testing during the main mode of ambulation elicits the highest oxygen uptake. Therefore the type of sports or daily locomotion determines whether the shuttle run, shuttle ride or a cycling test will be used (Bhambhani et al. 1992).

Children who are able to walk will be tested with an (adapted) shuttle run test (Léger and Lambert 1982; Verschuren et al. 2006). The speed of the shuttle run test will be adjusted based on the results of the muscle power sprint test and the agility test and the level of mobility, see Table 4.

In children with a congenital cardiopulmonary disease a cycling test will be used, because of the monitoring of the heart for safety issues. The cycling test, using the Godfrey protocol (Washington et al. 1994), will also be applied to evaluate the aerobic fitness in children who are active on a bike in sports or daily living. Load depends on height of the child and the expected level of fitness.

A shuttle ride test will be used in children using a wheelchair. Shuttle tests are field tests in which a participant walks or runs between 2 markers. In this case they have to ride a distance of 10 meters in their own wheelchair, if applicable their sports wheelchair, between two cones. The starting speed is 2.0 km/h and the speed is increased with 0.25 km/h every minute. The children have to keep on riding, until they fail to reach the cone two times in a row, despite encouragements. This protocol has been proven valid as a maximal exercise test in youth with CP and spina bifida (Verschuren et al. 2013; Bloemen et al. 2015).

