## Sample size

The sample size of the HAYS-study is based on a study of Verschuren and Takken (2010). In this study children and adolescents with cerebral palsy had an average peak oxygen uptake of 42 ± 8.2 ml/kg/min. To prove a difference of 10 % between sporting or non-sporting subjects, with an alpha of 0.05 and bèta of 0.20 (power of 0.80) a sample size of 66 subjects per group is required. When taking a failure rate of 10 % into account, 146 subjects should be included in total.

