## Discussion

The current paper describes the rationale, design and methods of a cross-sectional study concerning participation in sports focused on children and adolescents with a physical disability or chronic disease.

To our knowledge this is the first study to evaluate this effect of sport participation on physical, social and mental health within this population. The aim is to determine both the positive and negative effects of sports related to health outcomes in children with disabilities and chronic childhood onset conditions. We hypothesize that the group participating in sports regularly will show higher levels of physical activity associated with better health outcomes, a relative lower incidence density, better cognitive functioning and school performance.

New insights gained from this study could stimulate the improvement of facilities for adapted sports by the government. Also children with a chronic disease or physical disability and their caregivers, sport coaches, physical therapists and other interested parties will be more easily convinced of the advantages of sports participation for this population.

Although we carefully chose our study settings according to its population, we are aware of some limitations of the study.

Objective measurements are chosen where possible. To achieve the best results possible, the best fitting testing modality will be chosen for each participant. The testing modality has to mimic the type of sport participated in. In children who do not participate in sport, the most common form of physical activity in daily life will be chosen as an indicator for the test modality. In general, some test modalities have been proven to elicit a higher VO_2_ peak in the same subject (Bhambhani et al. 1992). The test modality could therefore influence the test outcome. To minimalize this bias we will pursue a comparable number of testing modality types in both groups.

In conclusion, this study will provide insight in the effects of sports participation on the health of children and adolescents with a chronic disease or physical disability.

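### VO2peak is measured with a mode, wheelchair and shuttle protocol that depend partly on sport participation; comparable modality counts plus an unadjusted test do not deal with this

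*Protocol article*

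**What the plan says.** Sample size: the calculation rests on peak oxygen uptake, from a study in which "children and adolescents with cerebral palsy had an average peak oxygen uptake of 42 ± 8.2 ml/kg/min". The aim is "To prove a difference of 10 % between sporting or non-sporting subjects", and "a sample size of 66 subjects per group is required".

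Discussion (limitations): for sporting children, "The testing modality has to mimic the type of sport participated in". For non-sporting children the commonest daily-life activity points to the mode. The same paragraph accepts that some modalities give a higher VO2peak in the same subject and that this could influence the outcome. The stated response is "To minimalize this bias we will pursue a comparable number of testing modality types in both groups".

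Aerobic fitness: type of sport or daily locomotion decides between shuttle run, shuttle ride and cycling. The same section assigns walkers to an (adapted) shuttle run, wheelchair users to the shuttle ride, and children with congenital cardiopulmonary disease, or who are active on a bike in sport or daily life, to cycling. The shuttle ride is done "in their own wheelchair, if applicable their sports wheelchair, between two cones". Shuttle-run speed is set from the muscle power sprint test, the agility test and the Table 4 level. The protocol is further adapted to expected fitness, with high competition level as one example and very low fitness as another.

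Physical fitness: the Functional Mobility Scale (FMS) at 500 m splits wheelchair users from walkers. Table 4 category IV is "Subjects with an excellent level of mobility, who are used to run at a speed of 8 km/h during their practicing their sports" or in competition.

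Design and Statistical analysis: matching is on gender, age and diagnosis. The group comparison is an independent-samples t-test or a non-parametric alternative.

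**The concern.** In a comparison of sporting with non-sporting children, the measurement should not depend on which group a child is in. Here three parts of it can: the test mode, the chair, and the shuttle level. If any of them moves VO2peak, part of the estimated difference is method rather than fitness, and more subjects will not reduce it.

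Comparable counts act on only one of the three. Two groups with the same numbers of shuttle runs, shuttle rides and cycle tests may still differ in who rides a sports chair and who gets the sport-defined shuttle level. Whatever imbalance is left passes straight into an unadjusted two-group estimate of the outcome on which the study is sized.

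**Working it through.** **1. The plan's own figure.** Inputs from Sample size: mean 42, SD 8.2, a 10 % difference (0.10 × 42 = 4.2 ml/kg/min), alpha 0.05, power 0.80. Sidedness is not stated, so two-sided is assumed.

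n per group = 2 × 8.2² × (1.960 + 0.842)² / 4.2² ≈ 60 (61 with the t distribution), against 66 stated. Rounding the difference to 4.0 gives 66 (67 with t). With 66 per group, power for 4.2 is about 0.84 (0.83 with t). The total follows: 132 × 1.10 = 145.2, rounded up to 146. The stated size is on the safe side, and this gap does not bear on the point here.

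**2. What decides each part of the measurement.**

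| Part | Depends on sport | Depends on something else | Addressed by comparable counts? |
|---|---|---|---|
| Mode (run, ride, cycle) | Mimics the sport; cycling if active on a bike in sport | FMS at 500 m, congenital cardiopulmonary disease, daily activity | Yes, on average, if achieved |
| Wheelchair | Sports chair if applicable | Own chair otherwise | No |
| Shuttle level | Category IV; competition level | Sprint and agility results, mobility, expected fitness | No |

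The mode rules also do not fully agree. For a child who walks 500 m but plays a wheelchair sport, the FMS split and the shuttle-run sentence point to the shuttle run, while the Discussion rule points to the shuttle ride.

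**3. Precision.** With 66 per group, SE of the difference = 8.2 × √(2/66) = 1.43 ml/kg/min.

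**4. Size under assumptions.** The documents give no figure for the effect of mode, chair or protocol level. If a share q of the sport group is shifted by a fraction m of the mean, bias b = q × m × 42. The two-sided rejection rate with no true difference is 1 − Φ(1.96 − b/SE) + Φ(−1.96 − b/SE).

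- q = 0.30, m = 0.03: b = 0.30 × 1.26 = 0.38; 0.38/4.2 = 9 % of target; rejection rate about 0.06.
- q = 0.30, m = 0.10: b = 0.30 × 4.2 = 1.26; 1.26/4.2 = 30 % of target; rejection rate about 0.14.

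**5. Sensitivity with equal modality counts**, where the shift arises within modality (chair, trained mode or protocol level):

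| m | q = 25 % | q = 50 % | q = 100 % |
|---|---|---|---|
| 5 % | b = 0.53, rate 0.066 | b = 1.05, rate 0.11 | b = 2.10, rate 0.31 |
| 10 % | b = 1.05, rate 0.11 | b = 2.10, rate 0.31 | b = 4.20, rate 0.84 |

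**6. Sensitivity with unequal counts.** A 5-15 % modality effect combined with a 10-30 percentage-point imbalance gives b from 0.05 × 42 × 0.10 = 0.21 to 0.15 × 42 × 0.30 = 1.89. That is 5-45 % of target, with rejection rates of 0.052 to 0.26.

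Steps 4 to 6 show what assumed shifts would do. They do not estimate the bias. The shifts are written as gains in the sport group, but the same sizes apply with the sign reversed.

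**The case against.** The authors disclose the limitation and promise only to reduce it. They have a reason for the habitual mode: the article cites evidence that it elicits the highest uptake, and each child, sporting or not, is tested in a familiar activity. The outcome is measured gas uptake at volitional exhaustion, not stage or distance. A faster chair or a different starting speed may therefore change the stage reached without changing VO2peak. Protocols are adapted at both ends of fitness to secure a minimum exercise time. Matching on diagnosis aligns some modality, and a fuller analysis plan may contain covariates.

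Much of this stands, and it limits what can be claimed. A reader might infer any of the following, and the documents do not support them:

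- That sport alone chooses the test. FMS, diagnosis, sprint and agility results also decide.
- That sporting wheelchair users get sports chairs and the others daily chairs. The text only permits a sports chair where applicable.
- That a non-sporting child can never reach category IV. The sport group is defined by organized sport at least twice a week for 3 months, so a child below that threshold may still run at that speed in sport.
- That the bias favours the sport group. This is plausible, but no direction is given.
- That the count aim contradicts the mode rule. Counts could be pursued through recruitment, although the article does not say how.

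The objection does not answer the gap in the remedy. Comparable counts leave chair type and protocol level untouched, and the comparison that the article does state carries any remaining imbalance into the estimate.

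**Conclusion.** The point holds in limited form. For the outcome behind the sample size, mode, chair and shuttle level depend partly on sport participation. The article admits that modality matters, and its only stated control covers one of the three elements, and that only as an aim.

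Neither size nor direction can be derived from the document. Assumed shifts of 3-10 % in 30 % of the sport group give 0.4-1.3 ml/kg/min, 9-30 % of the 4.2 target. The article admits an effect of modality; an effect of chair type or protocol level on gas-measured VO2peak is an assumption. This is a matter of measurement and analysis, and no change in sample size follows from it.

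**What to change.** 1. Keep the comparable-count aim, and record test modality and chair type for every child.
2. Compare VO2peak with a model that adjusts for, or stratifies by, modality and chair type, and report the group difference within each modality.
3. Define Table 4 category IV by running ability observed in the same way in both groups. The sprint and agility tests already performed can serve, as they already inform shuttle speed.
4. Reconcile the locomotion rule in Physical fitness and Aerobic fitness with the sport-mimicking rule in the Discussion, so that one rule applies to both groups. The cycling rule for congenital cardiopulmonary disease is not in question.

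The cost is some wording, one or two recorded items, a few degrees of freedom and some small strata; no extra test is needed. There is one limit. If nearly all sporting wheelchair users ride sports chairs and nearly all others daily chairs, adjustment cannot separate chair from sport in that stratum, and the report should say so.

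A single common mode or chair for all is an option the sponsor may weigh, not a required change, because it gives up testing in the habitual mode and may understate athletes' fitness.

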## Abbreviations

HAYS: Health in Adapted Youth Sports
MPST: muscle power sprint test
VO_2peak_: peak oxygen uptake
BIA: bioelectrical impedance analysis
BMI: body mass index
PWV: pulse wave velocity
AIX: augmentation index
QoL: quality of life
HRQoL: health related quality of life
FMS: functional mobility scale
SPSS: self-perception profile scale
